## Abstract

**Background:**

China has the largest burden of primary angle-closure glaucoma (PACG) worldwide. The mechanism of the angle closure is complex and includes pupillary block and non-pupillary block. Currently, opinion is that laser peripheral iridotomy (LPI) alone is not sufficient to prevent disease progression. Laser peripheral iridoplasty (LPIP) is an alternative and effective way of widening the angle recess in eyes that are affected by primary angle closure (PAC). However, it is not known if greater benefit would be achieved using LPI plus LPIP for PAC with multiple mechanisms (MAC). Thus, the aim of this study is to demonstrate if LPI plus LPIP would be more effective than single LPI in controlling the progression of PAC with multiple mechanisms, based on ultrasound biomicroscopy (UBM) classification. A secondary aim is to determine whether or not this would result in the use of less medication and/or prolong the time to antiglaucoma surgery.

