### Sample size

The sample size calculations are based on published PAC disease progression with LPI and LPIP treatment. Disease progression is defined as glaucomatous optic nerve injury, increased IOP for which antiglaucoma drugs are required, and PAS progression according to the published clinical trials [13–15]. It is assumed that the 3-year PAC progression rate after receiving LPI will be approximately 55%, and the rate for LPI plus LPIP will be 35%, with 80% statistical power and a two-sided test at 5% significance. Thus, allowing for 20% loss to follow-up, a sample size of 240 participants for this study is required (calculated using nQuery Advisor® + nTerim® 3.0 software; Statsols, Boston, MA, USA). There will be 120 patients in each treatment arm. The anticipated number of patients in the study (240) will be recruited over a 12-month period.

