### Primary outcome measures

The PAC progression rate will be determined by the number of patients in whom the disease progresses following laser treatment in each group within the 3-year follow-up period. PAC progression is defined as the presence of any of the following:Acute angle-closure crisis.An IOP measurement taken 1 month after the laser procedure that is 8 mmHg higher than that recorded at treatment initiation.An IOP measurement taken 1 month after the laser procedure that is ≥ 22 mmHg when measured three times in succession.The progression of PAS ≥ 1 clock hour within 3 years of the laser procedure, as determined by gonioscopy.Glaucomatous neuropathy within 3 years of the laser procedure.

Acute angle-closure crisis is defined as:The presence of at least two of the following symptoms: ocular or periocular pain, nausea and vomiting, blurred vision, and multicolored halos around lights (an occasional symptom).An IOP measurement of at least 22 mmHg, as measured by Goldmann® applanation tonometry.The presence of at least three of the following signs: conjunctival injection, corneal edema, a mid-dilated unreactive pupil, and a shallow anterior chamber.

Glaucomatous neuropathy is defined as:The documented progression of diffuse thinning and focal narrowing or notching of the optic disc rim.A cup disc ratio of ≥ 0.6.A cup-disc asymmetry ratio of ≥ 0.2 for similar-sized eyes or optical discs.Diffuse or localized abnormalities in the peripapillary retinal nerve fiber layer.The presence of glaucomatous visual field defect, defined as reproducible visual field defects, including nasal step, arcuate field defect, or paracentral depression in the clusters of the test sites.Visual field loss in the upper hemifield that is different to that in the lower hemifield.The absence of any other known explanation.

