### Data analysis

The statistical tests will be two-sided. A level of 0.050 will constitute statistical significance. A comparison of the normally distributed continuous variables between two groups, expressed as mean ± standard deviation, will be determined using two independent *t* tests. The natural logarithmic transformation will be applied to variables that are positively skewed. Non-normally distributed continuous variables, presented as the median and interquartile range, will be analyzed using the Wilcoxon rank-sum test. The ordinary variables, also presented as median and interquartile range or percentages, will be analyzed using Wilcoxon signed-rank test. Pearson’s chi-square test or Fisher’s exact test will be used, as appropriate, for the categorical data and expressed as percentages. If the primary outcome is not realized, the last observation carried forward method will be used to impute the reason why. Any other values will remain as absent. The baseline characteristics will be evaluated using intent-to-treat (ITT) analysis. Efficacy analysis will be applied to the ITT and per protocol populations. Reasons for loss to follow-up will also be presented.

An evaluation of the rate of disease progression after 3 years of follow-up will be conducted using efficacy analysis as the primary outcome measure. A comparison in this regard will be made between the LPI and LPI plus LPIP groups using Pearson’s χ^2^ test. Logistic regression analysis will be performed to evaluate the central effect and the progression rate adjusted to account for it.

The safety evaluation data, as per the secondary outcome, will be analyzed using a generalized linear model in consideration of any covariates or the central effect. Sensitivity analysis will be conducted to assess for heterogeneity. Statistical Analysis Software® 9.4 (SAS Institute Inc., Cary, NC, USA) will be used to analyze the collected data. The data analysis will be performed by personnel in the Department of Biostatistics, Southern Medical University, Guangzhou, China.

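### Last observation carried forward scores patients lost before an observed event as non-progressors, which lowers both 3-year progression rates and exposes the primary comparison to unequal loss

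*Protocol article*

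**What the plan says.** The Data analysis section of the protocol article states that, where the primary outcome has not been obtained, "the last observation carried forward method will be used to impute the reason why". The next sentence adds: "Any other values will remain as absent". Taken together, a missing primary outcome is filled by last observation carried forward (LOCF) and nothing else is imputed. Efficacy is analysed in the intention-to-treat and per-protocol populations, and the primary test is a Pearson chi-square on the 3-year progression rate. The only sensitivity analysis named concerns heterogeneity.

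Under Primary outcome measures, "PAC progression is defined as the presence of any of the following", followed by five criteria. The rate counts patients who progress "within the 3-year follow-up period".

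Under Sample size, the assumed 3-year rates are 55% (LPI) and 35% (LPI plus LPIP), with 80% power and a two-sided 5% test. The total is 240, "allowing for 20% loss to follow-up".

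**The concern.** A patient who meets any criterion before leaving already has the outcome, so nothing needs to be imputed. LOCF of status therefore acts on patients who leave event-free, and it carries forward the absence of progression. Someone lost at month 6 is treated as having no risk for the remaining 2.5 years, although the plan itself assumes 3-year risks of 55% and 35%. The error runs one way: each arm's rate can only fall.

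Two things follow. The analysis population no longer matches the one the trial was sized on, because lost patients return to the denominator, mostly as non-events. And the fall in an arm's rate grows with the share lost in that arm, so unequal loss moves the treatment difference even when the treatments are equally effective. The trial is open-label, so unequal loss is possible.

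**Working it through.** **Inputs from the protocol (Sample size).** Rates 0.55 and 0.35; two-sided 5% test; 80% power; 20% loss; 120 per arm.

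**Assumptions not in the protocol.** Constant progression hazard; leaving independent of progression; normal approximation. Three patterns of leaving are used: even over 0–3 years; confined to year 3; and a bound with all loss right after laser. The null rate of 45% is the midpoint of 55% and 35%.

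**1. The plan's own figure.** With pooled variance and no continuity correction:

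n = [1.96·√(2·0.45·0.55) + 0.8416·√(0.55·0.45 + 0.35·0.65)]² / 0.20² = (1.379 + 0.580)² / 0.04 = 95.9, so 96 per arm. Then 96 / 0.8 = 120 per arm and 240 in total, an exact match. The 20% are thus removed, and 96 per arm are evaluated at the full rates.

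**2. Reported rate under LOCF of status.** For true 3-year rate p, share lost d, and share m of leavers who progress before leaving:

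reported rate = (1 − d)·p + d·m

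With L = −ln(1 − p):
- even leaving: m = 1 − p/L
- year 3 only: m = 1 − (e^(−2L/3) − e^(−L))/(L/3)
- bound: m = 0

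*Equal 20% loss, even leaving*
- LPI: L = 0.7985, m = 0.311, rate = 0.440 + 0.2 × 0.311 = 0.502
- LPI plus LPIP: L = 0.4308, m = 0.188, rate = 0.280 + 0.2 × 0.188 = 0.318
- Difference 18.5 points instead of 20

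Power = Φ[(difference − 1.96·SE₀)/SE₁] at 120 per arm, where SE₀ is the pooled and SE₁ the unpooled standard error:
- even: (0.1847 − 1.96 × 0.0635)/0.0624 = 0.97, power 83.3%
- bound: rates 0.8 × 0.55 = 0.44 and 0.8 × 0.35 = 0.28, difference 16 points; (0.16 − 1.96 × 0.0620)/0.0611 = 0.63, power 73.6%
- year 3 only: 53.7% vs 34.0%, power 87.1%

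For reference, 96 completers per arm give 80.0%.

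**3. No true effect, 45% in both arms.** The spurious difference is (difference in loss) × (p − m). Here L = 0.5978, so m = 0.247 (even), 0.391 (year 3) or 0 (bound). For 30% vs 10% with even leaving this is 0.20 × (0.45 − 0.247) = 0.041.

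| Loss by arm | Pattern | Spurious difference (points) | Type I error |
|---|---|---|---|
| 20% vs 20% | any | 0 | 5.0% |
| 25% vs 15% | even | 2.0 | 6.2% |
| 25% vs 15% | bound | 4.5 | 11.2% |
| 30% vs 10% | even | 4.1 | 9.8% |
| 30% vs 10% | bound | 9.0 | 30.5% |
| 30% vs 10% | year 3 only | 1.2 | 5.4% |

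**4. True 55% vs 35% with unequal loss.** With 30% lost on LPI and 10% on LPI plus LPIP, the difference is 14.5 points and power 62.7% (even), or 7.0 points and 20.5% (bound). With the imbalance reversed, the 20-point effect is reported as 22.5 points (even) or 25.0 points (bound).

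**The case against.** The strongest reply is that the planned case is benign. The protocol allows for 20% loss and names no imbalance. With equal loss type I error stays at 5%, the difference shrinks toward zero (conservative for a superiority trial), and under even leaving power is 83.3%, above the planned 80%. All of that stands. It does not rescue the reported rates, and it relies on balance and timing that cannot be known in advance.

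Several stronger readings are tempting but not supported:

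- *That nearly every patient who leaves is scored a non-progressor.* Under even leaving, about 31% of LPI and 19% of LPI plus LPIP leavers progress first and stay counted. The bound of 44% vs 28% needs all loss to occur right after laser.
- *That any imbalance produces a false or hidden effect.* Any imbalance biases the difference, but not always materially: 22.5% vs 17.5% loss with even leaving gives a type I error of 5.3%. Nothing in the protocol points to 30% vs 10%. Table 1 has one laser day and one visit schedule for both arms, so the extra procedure adds no later visits.
- *That the direction is certain.* The sentence does not say whether LOCF works on the composite or on its components. A carried-forward high IOP could falsely satisfy the criterion of three consecutive readings and create an event, which is the opposite error.
- *That the plan wrongly lacks a time-to-event method.* The abstract speaks of whether treatment would "prolong the time to antiglaucoma surgery", but the secondary outcome asks whether surgery is needed, not when. A method for that aim may sit in an analysis plan that is not shown.

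An unseen analysis plan may also add missing-data sensitivity analyses. The article nevertheless states LOCF as the rule for the primary outcome.

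**Conclusion.** The concern holds in this limited form. LOCF is a stated rule, not an omitted detail, and on its natural reading it gives event-free leavers no remaining risk. Both arms' rates are then too low, and the analysis does not match the 96-of-120 basis of the sample size. With equal 20% loss the cost is an understated rate and a difference of 18.5 points (even loss), or 16 points at the bound. The test remains valid, and power ranges from 74% at the bound to 83% with even loss and 87% if all loss is in year 3. Error-rate inflation requires unequal loss: slight for 25% vs 15% with even leaving, serious only if the imbalance is large, the leaving early, or both. These sizes rest on a constant hazard and on leaving unrelated to progression. The point should be fixed before the 3-year outcomes are analysed; it does not undermine the design.

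**What to change.** 1. Rewrite the garbled sentence so that it says what is imputed and at what level, and remove LOCF from the primary analysis.
2. Keep the 3-year proportion comparison, but multiply impute progression status after dropout by arm, IOP stratum, time of leaving and last observed measurements.
3. Add a tipping-point analysis showing how different the unobserved outcomes in one arm would have to be to change the conclusion.
4. Support this with a 3-year cumulative progression estimate by arm that censors leavers at their last assessment (Kaplan-Meier or interval-censored). State its non-informative-censoring assumption, since censoring alone does not cure outcome-related dropout.

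One practical check comes first. PAS progression is judged by gonioscopy, but Table 1 has no gonioscopy row. Confirm when it is done before relying on dated PAS events or on the last PAS value as an imputation variable.

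The cost is modest extra programming and a somewhat wider interval.

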### Randomization process

Patients will be randomly assigned to treatment with either single LPI or LPI plus LPIP using a 1:1 ratio via an online central randomization system. (This system is run by personnel in the Department of Biostatistics, Southern Medical University, Guangzhou, China), using the IOP as the stratification parameter. Patients will be stratified into a high IOP subgroup (21 mmHg to ≤ 30 mmHg) and a low IOP subgroup (≤21 mmHg) since it is likely that IOP will vary in the enrolled PAC participants. This procedure will ensure that there is a nearly equal number of patients in each treatment group early on in the trial and that the investigator will not be able to predict the next treatment assignment. In addition, the number of patients in the high and low IOP arms will almost be equal. The intervention date is the study entry date. Dates for all postoperative follow-up visits will be computed from this date.

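### Randomisation is stratified by IOP but the primary test ignores the stratum, so the test is valid but somewhat conservative; the printed strata also both contain 21 mmHg

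*Protocol article*

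**What the plan says.** **Design.** The Randomization process section allocates 1:1 through a central online system, "using the IOP as the stratification parameter". No other stratification factor is named. The high stratum is printed as 21 up to and including 30 mmHg, and the low stratum as 21 mmHg or less. The section adds: "In addition, the number of patients in the high and low IOP arms will almost be equal".

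**Analysis.** The Data analysis section takes the rate of progression after 3 years as the primary outcome: "A comparison in this regard will be made between the LPI and LPI plus LPIP groups", by Pearson's chi-square test. A logistic regression then evaluates the centre effect and adjusts for it; the abstract says the same. IOP stratum is in neither. Covariates are mentioned only for the safety data.

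**Outcome.** Under Primary outcome measures, progression is any one of five events. One is an IOP of 22 mmHg or more on three successive measurements.

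**Sample size.** The assumed rates are 55% for LPI and 35% for LPI plus LPIP, "with 80% statistical power and a two-sided test at 5% significance"; "allowing for 20% loss to follow-up, a sample size of 240 participants for this study is required".

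**The concern.** The analysis does not follow the randomisation. The one factor that the design balances is left out of the primary comparison, while centre, which is not named as a stratum, is adjusted for.

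When allocation is balanced within strata, differences between strata no longer contribute to the chance difference between arms. Pearson's variance still counts them. If the stratum is prognostic, the standard error is therefore too large, the test rejects too rarely under the null, and it has less power than a test that uses the stratum. The factor is plausibly prognostic here: the strata divide at 21 mmHg, and sustained IOP one unit higher counts as progression.

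Two drafting faults in the Randomization process section bear on the remedy. A stratified analysis can be reproduced only if each patient belongs to one stratum, and an eye at exactly 21 mmHg fits both. The sentence on nearly equal numbers can also be taken to promise equal stratum sizes, which stratification does not deliver.

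**Working it through.** **1. The plan's own figure.** Inputs from the Sample size section: 55% versus 35%, two-sided 5%, 80% power, 20% loss. With pooled rate 0.45,

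n = [1.960·√(2·0.45·0.55) + 0.842·√(0.55·0.45 + 0.35·0.65)]² / 0.20² = [1.379 + 0.580]² / 0.04 = 95.9, so 96 per arm.

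96 / 0.80 = 120 per arm, 240 in total. The stated figure reproduces exactly. It is based on an unstratified comparison.

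**2. Assumptions that the article does not supply.** Two equal strata; allocation balanced 1:1 within each; the same stratum odds ratio (OR, high versus low IOP) in both arms; marginal rates held at 55% and 35% (45% in both arms under the null). The OR is not given, so a range is shown.

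**3. Type I error.** Write V for the pooled variance 0.45·0.55 = 0.2475 and W for the mean within-stratum variance. The true two-sided alpha of Pearson is 2·[1 − Φ(1.960·√(V/W))].

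Example, OR 4: the null stratum rates are 28.5% and 61.5% (mean 45%). W = (0.2039 + 0.2368)/2 = 0.2203. √(0.2475/0.2203) = 1.060, and 1.960 × 1.060 = 2.077, so alpha is 3.8%.

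**4. Power at 96 per arm.** Example, OR 4: stratum rates are 38.5% and 71.5% with LPI, and 20% and 50% with LPI plus LPIP.

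- True standard error of the difference: √((0.2203 + 0.2050)/96) = 0.0666.
- Pearson uses √(2·0.2475/96) = 0.0718. Power = Φ((0.20 − 1.960·0.0718)/0.0666) = 81.3%.
- The Cochran-Mantel-Haenszel (CMH) test uses the mean of the pooled within-stratum variances, 0.2227: √(2·0.2227/96) = 0.0681. Power = Φ((0.20 − 1.960·0.0681)/0.0666) = 84.1%.

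| Stratum OR | True alpha, Pearson | Power, Pearson | Power, CMH | Gap (points) | Gap in simulation |
|---|---|---|---|---|---|
| 1 | 5.0% | 80.0% | 80.0% | 0 | 0 |
| 2 | 4.7% | 80.4% | 81.1% | 0.7 | 0.3 |
| 3 | 4.2% | 80.9% | 82.7% | 1.8 | 1.6 |
| 4 | 3.8% | 81.3% | 84.1% | 2.8 | 2.9 |
| 6 | 3.1% | 82.2% | 86.5% | 4.3 | 4.4 |

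The simulation used 400,000 trials per scenario. It gave the same Pearson alphas to within 0.1 point, and the CMH test stayed between 4.8% and 5.0%. With all 120 per arm analysed, the formula gives Pearson versus CMH power of 88.4% versus 88.9% (OR 2), 88.9% versus 90.1% (OR 3) and 89.3% versus 91.2% (OR 4).

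**5. Patients at exactly 21 mmHg.** The article gives no IOP distribution. Assuming a normal distribution with mean 18 to 21 and SD 4 to 5, and readings rounded to whole mmHg, the expected count is 240·[Φ((21.5 − mean)/SD) − Φ((20.5 − mean)/SD)]. This runs from 16.0 (mean 18, SD 5) to 23.9 (mean 21, SD 4), so about 16 to 24 of 240.

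**The case against.** The strongest reply is that nothing is broken: the test is valid, the trial was sized for this unstratified comparison, and the article gives no stratum-specific rates. Only one of the five progression criteria is a sustained fixed IOP threshold. The rise of 8 mmHg is relative to the patient's own starting value, and PAS progression and neuropathy are not defined by IOP. Patients can also enter through PAS without raised IOP, so PAS progression might raise risk in the low stratum. This stands: the strength of the association is an assumption, and a stratum OR near 1 would leave almost nothing to gain.

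Stronger readings are tempting, and the documents do not support them:

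- *The trial loses planned power, or 240 is wrong.* Pearson keeps 80.0% to 82.2% power over ORs of 1 to 6. What is forgone is extra efficiency.
- *The p-values cannot be trusted.* The error is on the conservative side. Type I error is not inflated, and a significant result would stand.
- *The test is severely conservative.* Null stratum rates of 80% and 10% would give a true alpha near 0.6%, but that is an OR of 36 (0.8·0.9 / (0.1·0.2)), and nothing in the article suggests it.
- *The equal-numbers sentence is false.* It follows a sentence on balance between treatment groups and can be read as balance of arms within each stratum, which is correct. It is ambiguous.
- *The overlap biases the comparison.* Allocation is random in whichever stratum a patient is placed.

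It can also be said that an unseen analysis plan may add the stratum to the logistic model. It may, but the article itself fixes Pearson's chi-square as the primary test, and that is the point at issue.

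**Conclusion.** The point holds as a modest matter of efficiency plus a drafting correction. The primary test omits the only stated stratification factor. If IOP stratum is prognostic, the test is conservative by about 0.3 to 1.9 points of alpha and gives up about 0.7 to 4.3 points of power against a stratified test, over stratum ORs of 2 to 6. These sizes rest on equal strata, balanced allocation, a common OR and 96 evaluable patients per arm; the OR itself is assumed.

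The overlap at 21 mmHg is plain in the printed definitions and does not depend on those assumptions; only the count of patients concerned does.

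**What to change.** - Make the primary ITT analysis a CMH test stratified by the IOP stratum as randomised, and report a stratum-weighted risk difference with its confidence interval. A logistic model with arm, IOP stratum and centre is an acceptable alternative. Name one of them as primary.
- Keep Pearson's chi-square as a supportive analysis.
- Restate the IOP strata without overlap, exactly as coded in the randomisation system, so that the text and the recorded strata agree.
- Reword the equal-numbers sentence to say that stratification balances the arms within each stratum and does not set the stratum sizes.

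**Cost.** The analysis change is wording only, with no added patients or data. Restating the strata requires a check of the randomisation system's coding, since the Trial status section reports that more than a quarter of the sample has been recruited. The analysis change should be fixed before outcome data are compared by arm.

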## Discussion

LPI alone is not considered to be sufficient to treat the large number of PAC patients with multiple mechanisms of angle closure in China. Laser treatment, based on the type of angle closure, is reasonable and necessary. A multicenter, prospective, randomized controlled trial on the optimal laser treatment for PAC is mandatory but is currently lacking. This trial is the first multicenter, prospective, randomized controlled trial that will evaluate the effect and safety of LPI plus LPIL, compared with LPI alone, for the treatment of PAC with multiple mechanisms based on UBM classification. The findings are expected to provide evidence that laser treatment for PAC should be based on the mechanism of angle closure.

Strengths of this trial include the fact that UBM-based angle-closure classification will be used, central randomization will be applied, the IOP will be classified as high and low, and the follow-up will be over a long term (3 years).

It was found by Jiang et al*.* that a thick peripheral iris was more relevant to a narrow angle configuration, based on UBM images in Chinese patients, although the anterior rotation of the ciliary body and the iris insertion was similar to that in narrow- and wide-angle eyes. However, on the other hand, it was demonstrated that multiple mechanisms were involved in angle closure in Chinese PAC patients [16].

Thus, the use of laser treatment (LPI plus LPIP), based on the UBM classification in the current study, was prudent. Though our previous randomized controlled trial stated that the use of LPI plus PLPI achieved an equivalent reduction in IOP in PAC and PACG, in that study both PAC and PACG patients with PAS were included and the type of angle closure was not classified, which may have influenced the results [13].

The classification of angle closure, based on the UBM images, is an issue that requires attention. Since there is no unified guideline on the UBM classification of angle closure, we referred to the previous hospital-based population study and the Liwan Eye Study carried out at Zhongshan Ophthalmic Center [5, 16]. Since UBM classification is semiquantitative, we used UBM analysts to avoid possible bias.

